## Protocol

# [name], [name], [name], [name], [name]

1. **Background**

In order to evaluate the quality (internal validity) of randomized controlled trials assessing NPT 1, 2(e.g., surgery, technical operations, angioplasty, joint lavage, use of technical devices, radiotherapy, transcutaneous electrical nerve stimulation, rehabilitation, behavioural therapy, natural health practices (yoga), and psychotherapy) a checklist of items was developed using the Delphi Consensus Method.3, 4

This checklist, called CLEAR NPT, includes 10 items and 5 sub-items and is presented with a “users’ guide” explaining in detail the meaning of each item.

1. **Objective**

To develop a computer learning system (CLS) to train physicians and/or systematic reviewers to use the CLEAR NPT checklist.

1. **Method**

) “Review”

*Method: We reviewed the literature about CLS used for personal and didactic training in:

-Pub Med using the words “computer assisted instruction”, “computer assisted learning system”, “Integrated learning system” 5-8

-The Cochrane library using the same words as used previously

-ERIC (educational resources information center)

-Psyclit

-Embase (excerpta medica)

-Yahoo: searching for “computer assisted instruction”, “computer assisted learning”,

“knowledge based expert system”

*Result: we selected “20” papers5-25 that showed the type of CLS system used in medicine and other fields and the common process of assessing their validity and reliability.

) Practicing CLEAR NPT

We selected a number of 40 reports (randomized controlled trials using non pharmacological treatments).

A group of 2 people (IB, LF) [One involved in the elaboration of CLEAR NPT, one using it for the first time] assessed the reports using the CLEAR NPT items.

Then we listed difficulties encountered during this process (lack of comprehension of the items, lack of data in the text, main issues to understand the question proposed by each items…etc…).

Regarding these difficulties, we selected text from these reports that a reviewer would question when using CLEAR NPT; these passages became the database of the computer program.

) Designing the program

We designed a computer program following the model of a knowledge-based expert system.

We first entered the database in the program.

We then designed for each item a chain of possible answers and consequences based on this model:

The first item is proposed to participants (with an adequate sample of reports)

Wrong answer Right answer Explanation of the answer

based on the “user’s guide”

previously given to the participants

A sub-item is to enhance memorization of the item

proposed to respondents and its possible answers.

to improve the understanding

of the previous item

This sub-item can be a list of Second item is proposed

questions giving details about

the first item (i.e., which question

should one ask when reading

the first item).

Right answer to Wrong answer to the sub-item

the sub-item

User guide slide Another Explanation of the answers of items

explanation of the sub-item is AND sub-items based on the “user’s

correct answer for designed guide”

this example, then

go to the next item

Explanation for this item

User guide slide

Then go to the next item

This program should enhance the understanding and the proper use of the CLEAR NPT by stimulating the reflexion of participants who can understand their own mistakes and correct them spontaneously.

) Evaluation

**Study design**: Randomised controlled trial comparing two groups of participants:

-intervention group: trained with the computer learning system,

-control group: no specific training

**Participants**: All the Cochrane Review Groups will be invited to participate. Reviewers who published a Cochrane review will also be invited to participate in this trial.

The randomisation will be centralized in the Department of Clinical Research at Hospital Bichat.

Reviewers agreeing to participate will be randomised according to a computer-generated randomisation list. Reviewers randomised in the intervention group will receive an e-mail with an internet link to the CLEAR NPT and its user’s guide and a log-in for the computer learning system. Training takes between 30 to 45 minutes.

The control group will receive a link to the CLEAR NPT and its user’s guide.

All participants will have to assess 2 reports, one evaluating surgical procedures and the other evaluating participative interventions.

**Primary outcome**: The primary outcome will be the rate of correct answers for each group compared to a gold standard.

This gold standard will be determined by a consensus of 3 reviewers (LF, IB, PR) who will independently assess the panel of reports that will be evaluated by the participants.

This panel of reports will be randomized among all randomized control trials assessing nonpharmacological treatments and published in 2005-2006 in the following journals:

New England Journal of Medicine, JAMA, Lancet, Annals of Internal Medicine, BMJ,

Annals of Surgery, British Journal of Surgery, Annals of Surgical Oncology, Archives of General Psychiatry, American Journal of Psychiatry, Journal of Clinical Psychiatry, Physical Therapy, Supportive Care in Cancer, Archives of Physical Medicine and Rehabilitation

We will randomise reports, ensuring that half will concern surgical treatments and half participative interventions such as psychotherapy, rehabilitation, or diet

**Secondary outcome**: -rate of correct answers for each item

-qualitative assessment of knowledge-based expert system

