**Sample size calculation**:

According to the literature, we expect a rate of correct answers of 0.75 (SD: 0.15) in the control arm.26

10 participants are necessary in each arm to demonstrate a difference of 0.15 with a power of 80% at the 0.05 level of significance.

The sample size was raised to 20 participants per arm considering the clustering effect for readers and the rate of possible non-response after randomisation.

The statistical analysis will involve a random effects model to take into account the reader effect and the article effect.

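### Optional gain in precision: one reader characteristic recorded before randomisation, used as stratum and covariate, could take some between-reader variance out of the arm comparison; the planned analysis is valid without it

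*Protocol*

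**What the plan says.** Protocol, Method, Evaluation, Participants: "Reviewers agreeing to participate will be randomised according to a computer-generated randomisation list". The arms are training and no specific training, so a reader belongs to one arm throughout. Recruitment is through the Cochrane Review Groups, and "Reviewers who published a Cochrane review will also be invited to participate in this trial". On workload, "All participants will have to assess 2 reports, one evaluating surgical procedures and the other evaluating participative interventions". The section names no stratification factor and no reader characteristic to be recorded before allocation.

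Protocol, Sample size calculation: "we expect a rate of correct answers of 0.75 (SD: 0.15) in the control arm", and "10 participants are necessary in each arm to demonstrate a difference of 0.15 with a power of 80% at the 0.05 level of significance". Then: "The sample size was raised to 20 participants per arm considering the clustering effect for readers and the rate of possible non-response after randomisation". On analysis: "The statistical analysis will involve a random effects model to take into account the reader effect and the article effect". No reader-level covariate is mentioned.

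**The concern.** The protocol expects readers to differ in accuracy. It responds in two ways: a random reader effect, and larger arms, chosen partly for reader clustering. Neither removes the differences between readers from the comparison.

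- **Random intercept.** In a crossed design, where each reader worked under both conditions, the reader term would cancel from the contrast. Here readers are nested in arm, so the intercept makes the standard error honest and leaves the reader variance inside it.
- **Larger arms.** More readers shrink the standard error by averaging over more people. The variance per reader is unchanged.

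Only a characteristic that predicts accuracy and is known before allocation can take part of that variance out. What is at stake is some precision and the balance of the arms in a trial of about 40 people. The timing matters: a covariate term can be left to a statistical analysis plan, but a list cannot be stratified once it has been used. Experience asked for afterwards would also be missing for the non-responders whom the protocol anticipates.

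**Working it through.** **Inputs from the protocol:** control rate 0.75, SD 0.15, difference 0.15, alpha 0.05 (taken as two-sided; the protocol does not say), 20 per arm, 2 reports per reader, a checklist of 10 items and 5 sub-items. **Assumptions not in the protocol:** the accuracy gap between experience levels, an even split of readers between levels, and which SD the 0.15 is.

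**1. The plan's own figure.** For two independent means, n = 2 × (1.96 + 0.84)² × (0.15/0.15)² = 15.7, so 16 per arm, or 17 with the t distribution. The stated 10 is not reproduced; power at 10 per arm is 56% (t). A figure near 10 does appear if 0.15 is the SD per report, averaged over two reports with low within-reader correlation: for correlations of 0 to 0.3 the normal formula gives 8 to 11. The protocol does not state that reading, so both are carried below.

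**2. Mechanism.** With readers nested in arm, Var(difference) = 2 × (reader variance + within-reader variance/2)/n. The reader variance stays in full.

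**3. SD 0.15 as the SD of a reader's mean.** SE at 20 per arm = 0.15 × √(2/20) = 0.0474; two-sample t power 86.9%. A 50:50 factor with accuracy gap g explains (g/2)² of the variance, so R² = (g/2)²/0.15² = (g/0.30)² of the total. The residual SD is 0.15 × √(1 − R²), and one degree of freedom is lost.

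| Gap g | R² | SE, 20 per arm | Power, 20 per arm | Power, 17 per arm |
|---|---|---|---|---|
| unadjusted | – | 0.0474 | 86.9% | 80.7% |
| 0 | 0 | 0.0474 | 86.8% | 80.6% |
| 0.05 | 0.028 | 0.0468 | 87.8% | 81.7% |
| 0.095 | 0.10 | 0.0450 | 90.1% | 84.5% |

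R² = 0.2 would need a gap of 0.30 × √0.2 = 0.134, and R² = 0.3 a gap of 0.164, against a training effect of 0.15.

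**4. SD 0.15 as the SD per report.** Answer-level variance per report is 0.75 × 0.25/m.
- m = 10 answers: 0.01875, so reader variance is 0.0225 − 0.01875 = 0.00375 (17%). The SD of a reader's mean is √(0.00375 + 0.01875/2) = 0.115. Power at 20 per arm is 98.1%, and 98.3% if the factor explains 10% of reader variance.
- m = 15 answers: 0.0125, so reader variance is 0.0100 (44%). The SD of the mean is √(0.0100 + 0.0125/2) = 0.127. Power is 95.2%, and 96.2% with 10% of reader variance explained.

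**5. Adjustment or stratification?** The two were separated by simulation at 20 per arm with all variance between readers. R² = 0.3 was used so that the split is visible, not because it is likely. Adjustment alone lowers the mean SE from 0.0475 to 0.0401 and raises power from 87% to 95%. Stratifying as well gives 0.0395 and 96%. Stratifying without adjusting leaves the reported SE at 0.0475.

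**6. Chance imbalance.** For a 50:50 factor on an unstratified 20:20 list, the exact hypergeometric probability of a gap between arms of 30 percentage points or more is 11.3%; for 20 points or more it is 34%.

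**The case against.** The strongest reply is that nothing here is wrong. The random-effects analysis is valid, power at 20 per arm is about 87% or more, and most of the gain comes from a covariate term that an analysis plan not shown here may already contain. That stands, and it is why this is an improvement and not an error. What remains for the protocol is recording the variable before allocation and building the list.

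A reader might infer more from the text than it supports:

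- *That the random effect is the only provision for reader differences.* It is not; the arms were also enlarged, partly for clustering.
- *That the protocol decided against stratification.* It says only that the list is computer-generated. Silence about strata is not a decision.
- *That stratifying and adjusting are sure to remove variance.* No figure in the protocol links experience to accuracy with this checklist, and all invitees are Cochrane reviewers, so the range of experience may be narrow. With no association there is no gain.
- *That power would rise to 93% or 96%.* Those figures need R² of 0.2 or 0.3 of the total variance, hence an accuracy gap close to or above the whole training effect from one yes/no factor.
- *That chance imbalance adds a separate bias.* At R² = 0.2 the difference shifts by 0.042 or more in 1 trial in 20 (1.96 × √0.2 × 0.15 × √(2/20)). This is ordinary sampling error, already within the unadjusted SE of 0.0474, and cannot be counted again beside the loss of power.
- *That recruitment stream is a ready-made stratum.* The protocol does not say that the streams are exclusive, and a Review Group member may also be a published author.

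**Conclusion.** The mechanism holds: the plan leaves all between-reader variance in the standard error and names no baseline characteristic that could reduce it. The size is small and uncertain. If 0.15 is the SD of a reader's mean, the gain at 20 per arm runs from none to about 3 points of power for accuracy gaps up to 0.095, and to about 4 points at 17 completers per arm. If it is the SD per report, the gain is about 1 point or less when the factor explains 10% of reader variance. These figures assume two levels of equal size and a two-sided test.

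The gain has most use if non-response is appreciable. On the reader-mean reading 17 per arm are needed, so 20 leaves a reserve of about 3, and unadjusted power falls below 80% at 16 (78.1%). Stratification contributes mainly balance, which in a trial of 40 is worth having for its own sake.

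**What to change.** Before the list is used:

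1. Ask each reviewer at sign-up for the number of Cochrane reviews published, and split it into two levels at a cut fixed in advance. Use this in place of recruitment stream. Keep to one binary factor, given about 40 readers.
2. Generate the list in permuted blocks stratified by that factor.
3. Enter the factor as a fixed effect in the planned model, beside the reader and article effects. Stratifying without this term would forgo most of the gain.

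The cost is one sign-up question, a stratified list and one degree of freedom. If experience proves unrelated to accuracy, the loss is about 0.1 point of power (86.9% to 86.8% at 20 per arm, 80.7% to 80.6% at 17). No extra readers or reports are needed. Stating whether the SD of 0.15 refers to a report or to a reader's mean would also show which of the two sets of power figures applies.

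### The test panel is drawn from all eligible 2005-2006 trials without excluding the 40 reports that supplied the training program, so overlap that would tend to favour the trained arm is not ruled out

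*Protocol*

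**What the plan says.** **Training material.** Under *Practicing CLEAR NPT*: "We selected a number of 40 reports (randomized controlled trials using non pharmacological treatments". The same section continues: "we selected text from these reports that a reviewer would question when using CLEAR NPT; these passages became the database of the computer program". The section gives no publication years or journals for these reports.

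**How the program uses it.** The flow chart under *Designing the program* starts: "The first item is proposed to participants (with an adequate sample of reports". It then leads through right and wrong answers to an explanation of each.

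**Who sees it.** Under *Evaluation, Participants*, the intervention arm receives a log-in to the program. For the other arm: "The control group will receive a link to the CLEAR NPT and its user’s guide".

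**Test material.** Under *Evaluation, Primary outcome*: "This panel of reports will be randomized among all randomized control trials assessing nonpharmacological treatments and published in 2005-2006", followed by a list of 14 journals. The only further restriction is the type of intervention: "We will randomise reports, ensuring that half will concern surgical treatments and half participative interventions". Each reader takes one report of each type: "All participants will have to assess 2 reports, one evaluating surgical procedures and the other evaluating participative interventions".

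**Outcome.** "The primary outcome will be the rate of correct answers for each group compared to a gold standard".

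**The concern.** The training reports and the test reports are the same kind of document, and no rule separates them. The frame is set in the protocol itself, with the word *all*, so this is not a detail left open for an analysis plan. Read literally, the rule admits any of the 40 training reports that meets the year and journal criteria.

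The trial is meant to show that training improves use of the checklist. If a test report also supplied passages to the program, a trained participant may recall a taught answer for those items instead of applying the checklist. A control participant cannot. The difference in correct answers would then mix recall with skill, and a reader of the results could not tell the two apart.

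The planned random effects model would not correct this. An article effect absorbs difficulty common to everyone who reads that article, whereas prior exposure acts in one arm only.

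**Working it through.** The protocol gives no figure for overlap, so there is none to reproduce. What follows shows how large the effect could be under stated assumptions.

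**Inputs from the protocol**
- 20 participants per arm and 2 reports each, so 20 × 2 = 40 intervention-arm readings.
- Control rate 0.75 and target difference 0.15 (*Sample size calculation*), so a trained rate of 0.75 + 0.15 = 0.90 if the program works as hoped.
- 40 training reports; a checklist of 10 items and 5 sub-items (*Background*).

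**Assumptions (not in the protocol)**
- K of the 40 training reports lie in a frame of N reports, in the same proportion in both strata. K may be 0.
- On an overlapping report, every answer becomes correct. This is a ceiling.

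**Formulas**
- Share of readings affected: s = K/N.
- Expected affected readings: 40 × s.
- Largest rise in the trained-arm rate: s × (1 − baseline). This is s × 0.10 from a 0.90 baseline (program works as planned) and s × 0.25 from a 0.75 baseline (training has no effect).

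| K / N | s | Readings of 40 | Ceiling, baseline 0.90 | Ceiling, baseline 0.75 |
|---|---|---|---|---|
| 0 / any | 0% | 0 | 0 | 0 |
| 10 / 500 | 2% | 0.8 | 0.002 | 0.005 |
| 10 / 200 | 5% | 2.0 | 0.005 | 0.0125 |
| 20 / 200 | 10% | 4.0 | 0.010 | 0.025 |

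At the top of this range the ceiling is 0.010/0.15 = 7% of the target difference from the 0.90 baseline, and 0.025/0.15 = 17% from the 0.75 baseline.

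**Partial exposure.** The program holds passages, not whole reports. If 2 of 10 items of an overlapping report had been taught, and errors were spread evenly over items, each ceiling is multiplied by 0.2. That gives 0.0004-0.002 from 0.90 and 0.001-0.005 from 0.75. The reduction is smaller if errors concentrate on the taught items. That is plausible, because the passages were chosen as ones a reviewer would question.

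**Small panel.** The panel size is not stated. If it were 4 reports and one overlapped, 25% of readings would be affected, with ceilings of 0.25 × 0.10 = 0.025 and 0.25 × 0.25 = 0.0625. With an overlap share of 2-10%, the chance that at least one of 4 reports overlaps is 1 − 0.98⁴ = 8% to 1 − 0.90⁴ = 34%. These larger values are therefore conditional; the expected inflation stays as in the table.

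**Extreme case.** If all 40 reports lay in a frame of only 100, s = 40% and the ceilings would be 0.04 and 0.10. Nothing in the protocol points to this case.

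**The case against.** The strongest reply is that no overlap has been shown. The years and journals of the 40 reports are unstated, and a report must meet both the two-year and the 14-journal limits to enter the frame. If none does, the risk is nil. This stands, and it is why the range starts at zero.

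A reader might infer that trained participants will be tested on reports whose answers they have already been given. The protocol does not support that. The program contains selected passages used item by item. Nothing says that each of the 40 reports supplied a passage, or that any report was covered for all items.

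A reader might also infer an inflation of about 0.06, or 40% of the target difference (0.0625/0.15 = 42%). That figure needs a four-report panel with one overlap, whole-report exposure and no training effect, all at once. From the 0.90 rate implied by the protocol's own target, the same case gives at most 0.025, or 17%.

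The direction of bias is likely rather than certain. Two people assessed the training reports, while the test standard is a consensus of three, so a recalled answer need not match it. On the other hand, two of the three carry the same initials as the training assessors, which makes a match more probable.

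Finally, those same two assessors might notice a repeated report. That is plausible, but it is not a written rule, and it does not override a frame defined as all eligible trials.

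**Conclusion.** The point holds as a gap in the definition of the sampling frame. The protocol does not exclude the training reports from the test panel and does not give the facts that would show exclusion to be unnecessary. Contamination is therefore possible but not demonstrated. Where it occurred, it would tend to favour the trained arm on the primary outcome.

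The size is unknown and starts at zero. With an assumed 2-10% of readings affected, the ceiling is about 0.002-0.010 from a 0.90 baseline or 0.005-0.025 from a 0.75 baseline, and lower if only some items were taught. These figures rest on assumed values of K and N, on equal overlap in both strata, and on every affected answer becoming correct. They do not suggest that the trial is invalid. They do justify a correction that costs almost nothing.

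**What to change.** Add to the paragraph on the panel of reports, under *Evaluation, Primary outcome*: *The 40 reports used to build the computer learning system are removed from the sampling frame before the panel is drawn.* If the panel has already been drawn, check it against the 40 references and replace any overlapping report by the next random draw within the same stratum (surgical or participative).

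The cost is one sentence and a check of 40 references against the sampling list. The sample size, the outcome and the analysis model do not change. If the check finds no overlap, recording that result documents that training and test material were separate.

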**Sample size calculation**:

According to the literature, we expect a rate of correct answers of 0.75 (SD: 0.15) in the control arm.26

10 participants are necessary in each arm to demonstrate a difference of 0.15 with a power of 80% at the 0.05 level of significance.

The sample size was raised to 20 participants per arm considering the clustering effect for readers and the rate of possible non-response after randomisation.

The statistical analysis will involve a random effects model to take into account the reader effect and the article effect.

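### The stated 10 participants per arm does not follow from a difference of 0.15 and an SD of 0.15, unless the SD is per report and a reader's two reports are nearly independent, which the protocol does not say

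*Protocol*

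**What the plan says.** The Evaluation part of the protocol describes a "Randomised controlled trial comparing two groups of participants", one trained with the computer learning system and one given no specific training. Each participant assesses two reports, and the primary outcome is the rate of correct answers against a gold standard.

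The sample size paragraph gives its inputs in one place. It says "we expect a rate of correct answers of 0.75 (SD: 0.15) in the control arm" and then "10 participants are necessary in each arm to demonstrate a difference of 0.15 with a power of 80% at the 0.05 level of significance". The next sentence reads "The sample size was raised to 20 participants per arm considering the clustering effect for readers and the rate of possible non-response after randomisation". The planned analysis is a random effects model with reader and article effects.

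The paragraph does not say whether the SD of 0.15 belongs to a participant's overall rate or to a single report assessment. It gives no SD for the intervention arm, no sidedness, no within-reader correlation and no non-response rate.

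**The concern.** A difference of 0.15 against an SD of 0.15 is a standardised effect of 1.0. The usual requirement for two independent groups at that effect size is 16 or 17 per arm, well above 10. Taken at face value, the paragraph claims 80% power for a number that delivers little more than half.

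The base figure also supports the next step. The protocol presents 20 as twice a sufficient number, with the second ten covering reader clustering and non-response. If the base is really 17, the margin is 3 per arm. Participants are reached by e-mail, and the protocol itself expects some not to respond, so the size of that margin matters for judging whether the trial can tolerate the losses it foresees.

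**Working it through.** **Inputs (protocol, sample size paragraph).** Difference δ = 0.15; SD σ = 0.15; power 80%; level 0.05; stated result 10 per arm, raised to 20. Two independent arms of equal size, and two reports per participant (protocol, Evaluation).

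**Assumptions added.** The SD is the same in both arms. The test is two-sided, with one-sided shown as well.

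**1. Trying to reproduce 10, with σ as the SD of a participant's rate.** The standardised effect is d = 0.15/0.15 = 1.0.

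- Normal approximation: n per arm = 2 × (1.96 + 0.8416)² / d² = 2 × 7.849 = 15.7, so 16. One-sided: 13.
- Two-sample t-test (noncentral t): 16.7, so 17. One-sided: 13.1, so 14.
- Two proportions, 0.75 against 0.90: 100 per arm, or 113 with continuity correction.

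None of these gives 10. A one-sample or paired t-test with d = 1.0 gives 9.94, so 10 (power 80.3%), but that formula does not fit two separately randomised groups. The match is suggestive only; the protocol does not name its formula.

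**2. Power at given numbers, same reading.** The noncentrality is d × √(n/2). At n = 10 it is √5 = 2.24.

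| Analysed per arm | Power, two-sided t-test |
|---|---|
| 10 | 56.2% (one-sided 69.4%) |
| 14 | 72.1% |
| 16 | 78.1% |
| 17 | 80.7% |
| 20 | 86.9% |

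For 10 per arm to reach 80%, the SD would have to be about 0.113, or the difference about 0.199.

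With 20 randomised per arm, 15% non-response leaves 20 × 0.85 = 17 (80.7%), 20% leaves 16 (78.1%) and 30% leaves 14 (72.1%).

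**3. The other reading: σ is the SD of one report assessment.** The mean of a reader's two reports has variance σ² × (1 + ρ)/2, where ρ is the within-reader correlation. At ρ = 0 the SD of that mean is 0.15 × √0.5 = 0.106; at ρ = 1 it is 0.15.

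| ρ | Readers per arm for 80% (t-test) | Power with 10 | Power with 20 |
|---|---|---|---|
| 0 | 9 | 84.8% | 99.2% |
| 0.1 | 10 | 81.4% | 98.6% |
| 0.2 | 11 | 77.9% | 97.8% |
| 0.5 | 13 | 68.5% | 94.5% |
| 1 | 17 | 56.2% | 86.9% |

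**4. Sensitivity to the equal-SD assumption.** The SD is given for the control arm only. Averaging the two variances, with σ per participant, an intervention SD of 0.10 gives 12.4, so 13 per arm; an SD of 0.05 gives 9.8, so 10. The intervention SD would therefore have to be about a third of the control SD to yield the stated figure, and the protocol says nothing of the kind.

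**The case against.** The strongest defence is that the per-report reading fits the rest of the paragraph better. Inflating for reader clustering makes sense only if the base calculation treated report assessments as independent. On that basis 10 participants supply 20 assessments per arm against 17 needed, 9 readers would suffice at zero correlation, and 10 is the smallest sufficient number at a correlation of 0.1. The SD of about 0.11 that 10 per arm requires is then roughly what averaging two reports produces.

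Much of this stands. A reader might infer that no interpretation supports 10, but step 3 shows that one does. A reader might also infer that the increase to 20 is nearly exhausted before clustering or non-response is considered. That is not supported either. On the participant reading, the reader effect is already inside the SD, so the 3 spare places need cover only non-response and any article effect. On the per-report reading, the base is 9 or 10 and the increase is available for its stated purpose.

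The defence does not rescue the sentence as written. The protocol speaks of participants being necessary and never says that the SD is per report. Ten also stops being enough at a correlation of 0.2, while the protocol itself expects clustering by reader.

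**Conclusion.** The point holds in a conditional form. For a two-arm comparison of participants with SD 0.15 of a participant's rate, 10 per arm is wrong: 17 are needed (14 one-sided), and 10 gives 56% power (69% one-sided). Ten is about right only under two unstated conditions, a per-report SD and a within-reader correlation of roughly 0.1 or less. Both results assume a common SD in the two arms.

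It would be tempting to conclude that the trial is too small. The documents do not support that. With full response, 20 per arm gives 86.9% power on the participant reading and at least that at any correlation on the per-report reading. What remains exposed is the tolerance for non-response: 15% on the participant reading. On the per-report reading there is more room; for example, 14 responders per arm still give about 84% at correlation 0.5.

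This is a stated sample size and power figure to correct, with no consequence for the recruitment target.

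**What to change.** Keep 20 per arm. Establish from the source cited for the control rate whether 0.15 is a per-participant or a per-report SD. Then restate the paragraph, giving the sidedness and the test used.

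- **If per participant:** replace 10 with 17 and drop reader clustering as a reason for the increase. State that 20 per arm gives 87% power with full response and at least 80% only up to 15% non-response (78% at 20%, 72% at 30%).
- **If per report:** state the assumed within-reader correlation ρ and compute the number of readers from the variance SD² × (1 + ρ)/2 (9 at ρ = 0, 11 at 0.2, 13 at 0.5, 17 at 1). State that 20 per arm gives at least about 87% power at any ρ with full response.

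In either case, give the non-response rate that the increase is meant to absorb. The new text should not settle the unit of the SD before the source has been checked, because a guess could replace one wrong statement with another.

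The cost is a few lines of protocol text and one look at the cited source. No extra participants are needed.
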